### *Remote vs In-Person Care Analysis*

During our prior RCT of home hospital, patients experienced a mean of 0.09 (SD 0.29) adverse events during their home hospital admission. We believe the smallest clinically meaningful treatment difference would be 0.1 adverse events (i.e., from 0.09 to 0.19 adverse events per patient). In this non-inferiority trial ( $\alpha=0.025$ , power 80%, non-inferiority limit 0.1 events), we would require 210 patients (105 in each arm). Because of clustering, the actual required sample size will be larger. With 5 home hospital physicians ( $\rho$  0.01), we require 260 patients (130 in each arm). We consistently enroll 25 patients monthly, leaving us with sufficient power after about 11 months.

We plan an interim futility analysis. After 130 patients have completed the remote vs in-person care study, we will calculate the difference in adverse event rates between the two arms. If the difference is 0.10 or higher (with the higher rate in the intervention arm), then we will stop the trial for futility. This rule will reduce the power about 2%.

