### *Remote vs In-Person Physician Care*

In a randomized controlled non-inferiority trial, we will test an in-person daily physician visit (“in-person care;” control) vs a daily physician visit conducted remotely via video facilitated by a care team member (“remote care;” intervention) for acutely ill patients who are home hospitalized. The primary outcome (dependent variable) is number of adverse events during the acute episode of care (see “Summarizing Adverse Events” table below). The primary predictor (independent variable) is study arm (in-person care vs remote care). We will assess the non-inferiority of the primary outcome with a generalized linear model using Poisson distribution, given the primary outcome is count data. Although we have multiple covariates of interest, we are cognizant of over adjustment. We plan to adjust for age, gender, race/ethnicity, PRISMA-7, education, and HOSPITAL score). We may include additional covariates if groups have significant differences at baseline.

Because patients in the intervention arm will receive at least some of their intervention through a “change agent” (in this case, a Home Hospital team) shared with other participants, we need to account for this in the analysis. We will therefore cluster by Home Hospital physician using general estimating equations.

Other outcomes will be analyzed in a similar manner, using Poisson regression for other “count” outcomes (e.g., number of new or worsening signs or symptoms per patient, days at home since discharge), multivariable logistic regression for binary outcomes (e.g., 30-day readmission, ED visit, PCP

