#### Summarizing Adverse Events

| Measure                                     |
|---------------------------------------------|
| Fall                                        |
| Delirium                                    |
| Potentially preventable VTE                 |
| New pressure ulcer                          |
| Thrombophlebitis at peripheral IV site      |
| CAUTI                                       |
| New Clostridium difficile                   |
| New MRSA                                    |
| New arrhythmia                              |
| Hypokalemia                                 |
| Acute kidney injury                         |
| Transfer back to hospital                   |
| Mortality (unplanned) during admission      |
| Mortality (unplanned) 30-day post-discharge |

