## Power analysis

### *Standard Home Hospitalization*

Our recent RCT data suggest that at 90% power, we will require 38 patients in each arm. However, we also have prespecified a smallest important difference of \$1000, for which we will need 144 patients in each arm at 90% power.

For 30-day readmission, we will require 110 patients in each arm at 90% power (23% vs 7%). If the effect size is indeed smaller, for example 23% vs 15%, we will need 528 patients in each arm. However, we will not be able to power around a smallest important difference of 3%, for which we would need 4006 patients in each arm.

For percentage with a safety event, we will require 641 patients in each arm at 90% power and 493 patients in each arm at 80% power (15% vs 9%).

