### *Early Transfer*

To calculate sample size, we used simulation in the PASS program (NCSS LLC, Kaysville, UT) comparing gamma distributed costs, with baseline data based on the home hospital RCT. With 324 patients in each arm of the study, even accounting for intraclass correlation by Home Hospital physician (intraclass correlation coefficient 0.01, cluster size 65), we will have 82% power to detect a relative decrease of 21% in total costs of care, smaller than the 27% decrease seen in this outcome in the Home Hospital RCT and close to the smallest reduction that would be considered clinically important. This sample size will also provide 80% power to detect a 43% reduction in readmission (again smaller than that seen in the Home Hospital RCT), and 81% power to detect non-inferiority for adverse events (assuming a baseline of 0.15 events per patient).

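### The planning SD of 0.29 for the remote-care trial is that of 0/1 data and allows for no patient with two events; at the stated alpha of 0.025, 105 per arm gives about 68 to 70% power, not 80%

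*Protocol*

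**What the plan says.** Under Remote vs In-Person Physician Care the protocol states: "The primary outcome (dependent variable) is number of adverse events during the acute episode of care". The analysis is a "generalized linear model using Poisson distribution, given the primary outcome is count data". The Summarizing Adverse Events table lists 14 items. They include clinical events such as fall, delirium, arrhythmia and acute kidney injury, and also "Transfer back to hospital".

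The power section for this trial takes its inputs from the earlier home hospital RCT, where "patients experienced a mean of 0.09 (SD 0.29) adverse events during their home hospital admission". With alpha 0.025, 80% power and a non-inferiority limit of 0.1 events, it arrives at 105 per arm. Allowing for five physicians and rho 0.01, it raises this to 130 per arm.

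Similar figures appear elsewhere in the power analysis with another meaning. For the home versus traditional hospital comparison the text reads "For percentage with a safety event, we will require 641 patients" per arm at 90% power, and "493 patients in each arm at 80% power (15% vs 9"%). There, 15 and 9 are percentages of patients. For early transfer the non-inferiority power is given "assuming a baseline of 0.15 events per patient". The Study endpoints table lists the number of adverse events, not the percentage of patients with one, as a secondary endpoint of the home versus traditional hospital comparison.

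**The concern.** The percentage of patients with any event and the mean number of events per patient coincide only if nobody has two events. The protocol moves between the two (9% and 0.09, 15% and 0.15) without saying which was measured.

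The items in the list can occur together. A patient sent back to hospital because of an arrhythmia or a kidney injury could score at least twice. If the planning SD comes from data without any repeats, it understates the variance of the count to be tested whenever repeats do occur.

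The consequence is loss of power. The confidence interval would be wider than planned, and a remote arm with no true excess of events would more often fail to show non-inferiority. This does not by itself create false claims of non-inferiority. It means that the 80% in the protocol is not what the design delivers.

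**Working it through.** **Inputs.** Mean 0.09, SD 0.29, margin 0.1, alpha 0.025, power 80%, 105 and 130 per arm, rho 0.01 and five physicians (Protocol, Power analysis, Remote vs In-Person Care Analysis). Earlier RCT: 91 patients after relaunch, preceded by a pilot of 21 (Protocol, The home hospital model and prior clinical studies). Assumptions of this check: alpha is one-sided and the true difference is 0.

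**1. The plan's own sample size.** n per arm = 2 × SD² × (z_alpha + z_power)² / margin².
- One-sided 0.025: 2 × 0.0841 × (1.960 + 0.842)² / 0.01 = 132.02, so 133.
- One-sided 0.05: 2 × 0.0841 × (1.645 + 0.842)² / 0.01 = 103.99, so 104; a t-based calculation gives 105.

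The stated 105 reproduces at one-sided 0.05 and not at the stated 0.025.

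**2. The clustered figure.** With 130 / 5 = 26 patients per physician and arm, the design effect is 1 + 25 × 0.01 = 1.25, and 105 × 1.25 = 131, close to the stated 130. In reverse, 130 / 1.25 = 104 effective patients per arm. So 130 clustered carries the same information as about 105 unclustered.

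**3. What an SD of 0.29 implies.**
- Yes/no variable at 9%: √(0.09 × 0.91) = 0.286, which rounds to 0.29.
- Poisson count with mean 0.09: √0.09 = 0.300.

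All data sets whose mean rounds to 0.09 and whose SD rounds to 0.29 were then enumerated with one patient having two events. The smallest has 235 patients (divisor n − 1) or 223 (divisor n). The relaunched RCT and the pilot together make 91 + 21 = 112. As an example, 4 events in 43 patients give SD 0.294 if they fall in four patients, and 0.366 if one patient had two of them. So the planning data contained no patient with more than one event.

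**4. Power at 105 per arm.** Power = Φ(0.1 / (SD × √(2/105)) − z_alpha).

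| SD | One-sided 0.025 | One-sided 0.05 |
|---|---|---|
| 0.29 (plan) | 70.5% | 80.3% |
| 0.30 (Poisson, mean 0.09) | 67.6% | 77.9% |

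At 104 effective patients (130 clustered) and 0.025 the values are 70.1% and 67.1%. With SD 0.30 and alpha 0.025, 142 per arm would be needed before clustering.

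**5. Repeat events (assumed range; the protocol gives no figure).** Hold the mean at 0.09 and let an affected patient have 1 + Poisson(L) events. Then P(any event) = 0.09 / (1 + L), and variance = P(any event) × [L + (1 + L)²] − 0.09².
- L = 0.25 (1.25 events per affected patient): 0.072 × 1.8125 − 0.0081 = 0.1224, SD 0.35, power 54% at 0.025.
- L = 0.5 (1.5 events per affected patient): 0.060 × 2.75 − 0.0081 = 0.1569, SD 0.40, power 45% at 0.025.

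**The case against.** The power section presents 0.09 as a mean number of events, not as a proportion. A true count in which nobody had two events has exactly this mean and SD, and then 9% of patients and 0.09 events per patient are both correct. Re-tabulation may return the same numbers. This stands: the yes/no origin is an inference that the document cannot settle.

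A reader might go further and infer that the planning rate is a mislabelled proportion, that 0.09 is too low for the count, and that the stated power therefore has nothing to do with the endpoint. The documents do not support this. The appendix safety table shows 5 transfers, 5 delirium, 2 pressure ulcers and 4 thrombophlebitis in 203 home patients, that is 16 / 203 = 0.079 events per patient. The list there is partial (fall, hypokalemia, kidney injury and post-discharge death are missing), so the full rate may be higher, but nothing shows 0.09 to be wrong.

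It can also be said that co-occurrence is not documented. No table crosses events by patient, and the data collection tables place arrhythmia, hypokalemia and kidney injury under heart failure, which may confine them to a subgroup. That is fair, and it is why the 54% and 45% are a range under assumption and not an estimate. With Poisson variance alone, the SD costs about 3 points.

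What the objection does not remove is that an SD below that of the protocol's own Poisson model was used, and that the stated alpha does not give the stated power even with that SD.

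**Conclusion.** The point holds in a limited form. The planning SD is that of 0/1 data, allows for no repeat events, and is slightly smaller than the planned model implies. At one-sided alpha 0.025, margin 0.1 and true difference 0, power is about 70% with SD 0.29 and 68% with SD 0.30, both for 105 per arm and for 130 per arm with a design effect of 1.25. Of the roughly 12 points missing from 80%, about 3 come from the SD and the rest from an alpha that does not match the sample size. Any larger loss depends on repeat events, whose frequency the protocol does not report.

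The double use of 9%/0.09 and 15%/0.15 is a separate labelling fault that can be seen in the text without any inference. For the home versus traditional hospital comparison it concerns a secondary endpoint only.

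**What to change.** - In Remote vs In-Person Care Analysis, tabulate the mean and SD of the count defined in Summarizing Adverse Events from the patient-level data already held (the earlier RCT and the home patients since 2018). Use at least the Poisson variance. Restate the power for 105 and 130 per arm at one-sided 0.025, with a short range for overdispersion.
- Before tabulating, settle whether "Mortality (unplanned) 30-day post-discharge" belongs in the count, since the primary outcome is limited to the acute episode.
- Label 0.09 here and 0.15 under Early Transfer as a mean count or as the proportion of patients with any event.
- Under Standard Home Hospitalization, either power the secondary endpoint as listed in the Study endpoints table (a number of events) or say that the calculation is for a proportion.

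The cost is one tabulation and a revised power paragraph. No change in enrolment is required. The downside is a stated power less favourable than 80%.

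### Remote vs in-person trial: the stated alpha (0.025), power (80%) and sample sizes (105 and 130 per arm) do not agree with one another

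*Protocol*

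**What the plan says.** The Remote vs In-Person Care Analysis paragraph of the protocol's Power analysis section gives these inputs:

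- Outcome: "patients experienced a mean of 0.09 (SD 0.29) adverse events during their home hospital admission".
- Margin: the "smallest clinically meaningful treatment difference would be 0.1 adverse events (i.e., from 0.09 to 0.19 adverse events per patient").
- Error rates and first result, after alpha is given as 0.025: "power 80%, non-inferiority limit 0.1 events), we would require 210 patients (105 in each arm").
- Clustering: "With 5 home hospital physicians" and rho 0.01, "we require 260 patients (130 in each arm").

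The paragraph does not say whether alpha is one- or two-sided, what true difference is assumed, or what cluster size is used. It adds an interim futility rule after 130 patients and says that rule costs about 2% of power.

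The Treatment Assignment section, citing these calculations, says that once 210 patients are enrolled, and if remote care is non-inferior, remote care may continue as a single arm. The Paramedic Analysis paragraph says that similar power calculations apply to that comparison.

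**The concern.** The count of adverse events is the primary endpoint of the remote-care comparison, which the protocol's endpoint table lists as a randomised non-inferiority trial. Its alpha, power, SD, margin and sample size are all printed in one paragraph, so a reader can check them against each other, and they do not fit. If alpha 0.025 is correct, the chance of missing non-inferiority when the arms are truly equal is nearer 30% than 20% under the protocol's clustering allowance. If the sample sizes and the 80% are correct, the calculation used a looser alpha than the one printed. The decision on continuing remote care depends on this test.

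**Working it through.** **Inputs.** From the protocol: SD 0.29, margin 0.1, power 80%, alpha 0.025, equal arms, five physicians, rho 0.01. Assumed: alpha is one-sided (usual for non-inferiority) and the true difference is 0.

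**Formula for a difference in means.** n per arm = 2 × (z for alpha + z for power)² × SD² / margin². Here SD²/margin² = 0.0841/0.01 = 8.41.

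**Clustering.** The cluster size is inferred as per-arm n divided by five physicians. The Early Transfer paragraph supports this: it uses the same intraclass correlation with cluster size 65 for 324 per arm, and 324/5 = 64.8. The design effect is then 1 + (n/5 − 1) × 0.01. At n = 130 it is 1 + 25 × 0.01 = 1.25; at n = 105 it is 1 + 20 × 0.01 = 1.20. If n0 is the unclustered size, solving for n gives n = 0.99 × n0 / (1 − 0.002 × n0).

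**Step 1: what reproduces the printed sizes.**

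| One-sided alpha | Power | (sum of z)² | Unclustered n per arm, normal | Same, t-based | Clustered n per arm |
|---|---|---|---|---|---|
| 0.05 | 80% | 6.183 | 103.99 | 105 | 129.99 |
| 0.025 | 70% | 6.172 | 103.81 | 105 | 129.71 |
| 0.025 | 80% | 7.849 | 132.02 | 133 | 177.59 |

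The first two rows both return the printed 105 and 130. The third row, which is what the paragraph states, returns neither.

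**Step 2: what the stated inputs require.**

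- Before clustering: 2 × 7.849 × 8.41 = 132.02, so 133 per arm (266 in total).
- With cluster size held at 26: 133 × 1.25 = 166.25, about 166 per arm.
- With cluster size growing with n: 177.59, so 178 per arm (356 in total).

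**Step 3: power at the printed sizes, one-sided alpha 0.025.** Power = Φ(0.1/SE − 1.96), with SE = 0.29 × √(2 × DE/n), where DE is the design effect.

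| Patients | Per arm | DE | Effective n per arm | 0.1/SE | Power |
|---|---|---|---|---|---|
| 210 | 105 | 1 | 105 | 2.499 | 70.5% |
| 210 | 105 | 1.20 | 87.5 | 2.281 | 62.6% |
| 260 | 130 | 1.25 | 104 | 2.487 | 70.1% |
| 260 | 130 | 1 | 130 | 2.780 | 79.4% |

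All four are before the protocol's own loss of about 2% for the futility rule.

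**Step 4: other readings at alpha 0.025 and 80% power.** Unclustered, per arm:

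- 0.025 read as two-sided (0.0125 per side): 160.
- Non-inferiority of proportions at 0.09: 129.
- Poisson variance of 0.09 (SD 0.30): 142.
- Forms built on 0.09 versus 0.19: 188 to 220.
- Log rate ratio: up to 312.

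None gives 105.

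**The case against.** The strongest counter-argument is that the final size is nearly right: 130 per arm is close to the unclustered 133, and power there is 79.4%. Patients are individually randomised, and if each physician treats patients in both arms, physician effects largely cancel in the arm contrast, so an inflation may not be needed. This stands as a possible justification for 260. It does not rescue the paragraph, which presents 130 as the figure after clustering and 105 as the figure before it. The Statistical methods section also commits to clustering by physician with estimating equations. Nor does it help at 210 patients, where power is 70.5% at best.

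A second objection is that no true difference is stated. A true difference of about 0.012 events in favour of remote care would give 105 per arm at alpha 0.025 and 80% power (0.1 − 0.29 × √(2/105) × 2.802 = −0.012). Nothing in the protocol suggests that assumption, and a difference favouring in-person care would raise the requirement.

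Two stronger readings are tempting and go too far. A reader might infer that the sizes can only have come from alpha 0.05. They fit alpha 0.025 with 70% power as well, so the document does not show whether alpha or power was mis-stated. A reader might also infer that the trial carries a 5% false non-inferiority rate. That rate is set by the level at which the test is run, and the only level stated is 0.025. It would be 5% only if the test were actually run at one-sided 0.05; otherwise the shortfall falls on power alone.

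**Conclusion.** The paragraph is wrong as written: alpha 0.025, power 80% and 105 or 130 per arm cannot all hold as derived. At one-sided 0.025 the unclustered requirement is 133 per arm, 27% above the printed 105 (133/105 = 1.27). Power at 260 patients lies between 70.1% and 79.4%, depending on whether the clustering inflation applies. At 210 patients it lies between 62.6% and 70.5%.

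The result rests on three readings that the protocol leaves open: alpha is one-sided, the true difference is 0, and cluster size is per-arm n over five. The unclustered mismatch needs only the first two, and a two-sided reading of alpha would widen it.

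**What to change.** Rewrite the power paragraph; no extra patients are needed. Choose one:

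- Keep one-sided alpha 0.025 and state that 260 patients give about 70% power under the clustering inflation. The figure of about 79% should be used only if the inflation is dropped with a stated reason that is squared with the planned clustering by physician.
- State one-sided alpha 0.05 in place of 0.025, if that is the level at which the test will be run. The printed sizes and 80% power then agree, and the accepted false non-inferiority rate is 5%.

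In either case, state the sidedness of alpha, the assumed true difference and the cluster size, and say whether the quoted power is before or after the futility rule. Reconcile the 210-patient decision point in Treatment Assignment with the 260 in the power section.

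The cost is protocol wording, plus either a less favourable stated power or a looser stated alpha. The choice should be settled before the data are analysed, because the non-inferiority conclusion can depend on it.

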## Treatment Assignment

- All patients will be offered home hospitalization.
- If patient/caregiver does not consent, the research assistant will ask the patient's permission to collect covariates, functional status, and a quality of life measure to determine generalizability of enrollment.

As an amendment to our current protocol, patients will be randomized (random sized blocks between 3 and 6 stratified by infection, heart failure, COPD/asthma, and other with concealed allocation) to remote care (intervention) versus in-person care (control) at the time of enrollment. Once 210 patients have been enrolled in this schema (see power calculations below), and if remote care is noninferior to in-person care, we will allow remote care to continue as a single arm while continuing other concurrent experiments.

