| Monitoring    | Wireless remote vital signs, telemetry, activity tracking, sleep tracking, predictive analytics for deterioration                                                                                                                                                                                                                                                                                                                                                                                                                                                                                                                                                                                                                             |

As denoted in the figure above, the physician will make at least one daily interaction with the patient. The nature of this interaction will be guided by the control versus intervention arm, and the physician's discretion. If the patient is in the control arm, the physician will make a daily in-person visit (usual care). If the patient is in the intervention arm, the physician sees the patient remotely via facilitated video, including near-real-time transmission of heart, lung, and abdominal sounds as needed. The nurse or paramedic seeing the patient will facilitate a physical exam and discussion with the patient. If the physician chooses for clinical purposes, s/he may still see the patient in-person. At the discretion of the physician, paramedic, and nurse, the physician can make additional visits should the patient's clinical condition require it. The nurse or paramedic will make at least two daily visits to the patient's home. At the discretion of the physician, paramedic, and nurse, the nurse or paramedic can make additional visits should the patient's clinical condition require it. This will be an ongoing twice daily discussion among clinicians, patient, and caregivers, as applicable.

As denoted in the figure above, a patient or clinician can initiate a video or in-person visit at any time.

As denoted in the figure above, a home health aide may be deployed. If deemed necessary by the home hospital attending, patient, and/or caregivers, the home hospital program can provide an on-demand home health aide that can provide care in 12 hour shifts.

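### The sample-size derivation for the remote vs in-person trial is wrong as written: 210 does not match the stated alpha, and the step to 260 rests on an unstated physician-by-arm assumption

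*Protocol*

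**What the plan says.** The Power analysis section (Remote vs In-Person Care Analysis) takes its inputs from the earlier trial, where "patients experienced a mean of 0.09 (SD 0.29) adverse events during their home hospital admission". It sets alpha at 0.025 with "power 80%, non-inferiority limit 0.1 events", and concludes "we would require 210 patients (105 in each arm"). It continues: "Because of clustering, the actual required sample size will be larger". With 5 physicians and an intraclass correlation of 0.01 it arrives at 260 (130 per arm), reached after about 11 months at 25 patients a month.

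Three other places bear on this:

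- Treatment Assignment randomises individual patients, "stratified by infection, heart failure, COPD/asthma, and other with concealed allocation". Physician is not a stratification factor. The same section ties the decision on remote care to 210 enrolled patients, not 260.
- Study visits and measured parameters lets the patient's arm determine the type of visit: "If the patient is in the control arm, the physician will make a daily in-person visit (usual care"), whereas intervention patients are seen by facilitated video. No text allocates physicians to an arm.
- Statistical methods (Remote vs In-Person Physician Care) justifies the adjustment by a care team shared among participants: "We will therefore cluster by Home Hospital physician using general estimating equations".

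**The concern.** The 260 is reached in two steps, and each needs its own justification. The base of 210 should follow from the stated alpha, power, SD and margin. The clustering step should reflect how physicians relate to the arms. When patients are randomised individually and each physician treats both arms, whatever a physician contributes equally to both arms largely drops out of the between-arm difference. A design effect that treats the arms as separate sets of clusters then needs a reason, and none is given.

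The power of a non-inferiority comparison on adverse events is at stake. If the base is too small, the clustering allowance is in effect paying for the alpha. The 260 then cannot be defended as 80% power with clustering allowed for.

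**Working it through.** **Inputs from the protocol.** SD 0.29; margin 0.1; alpha 0.025 (read as one-sided, as is usual for non-inferiority); power 80%; 5 physicians; rho 0.01. The true difference is taken as 0, which the protocol does not state.

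**Step 1: the base of 210.** Per arm, n = 2[SD(z_alpha + z_power)/margin]².

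- One-sided 0.05: 2 × [0.29 × (1.645 + 0.842)/0.1]² = 103.99, so 104 per arm (105 with a t-test). This reproduces 210.
- One-sided 0.025: 2 × [0.29 × (1.960 + 0.842)/0.1]² = 132.02, so 133 per arm, or 266. This does not reproduce 210.
- Other outcome models at 0.025 do not rescue it: a binary outcome with rate 0.09 needs 129 per arm, and a Poisson count with mean 0.09 in both arms needs 142.

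**Step 2: the move from 210 to 260.** Take a design effect 1 + (m − 1)rho with m = n/5 patients per physician per arm. Solving for n gives n = n0(1 − rho)/(1 − n0·rho/5).

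- n0 = 104: 102.96/0.792 = 130.0
- n0 = 105: 103.95/0.79 = 131.6

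So 130 per arm is 104 × 1.25, with m = 26. All five physicians appear in each arm, and their effects in the two arms are treated as unrelated.

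If the five physicians were instead each tied to one arm, m would be 2n/5. The same formula would then need about 176 to 179 per arm (353 to 359 in total). The protocol's 260 is therefore not that case.

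**Step 3: the factor when physicians see both arms.** Let r be the correlation between a physician's effects in the two arms. The protocol gives no value, so the full range is shown. The factor is 1 − rho + m·rho·(1 − r), evaluated at m = 26. Power for 130 per arm at one-sided 0.025 is Φ(0.1/(0.29·√(2·DE/130)) − 1.96), where DE is that factor.

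| r (assumed) | Design effect | Power at 260 |
|---|---|---|
| 1 | 0.99 | 79.8% |
| 0.9 | 1.02 | 78.8% |
| 0.75 | 1.06 | 77.2% |
| 0.5 | 1.12 | 74.8% |
| 0 | 1.25 | 70.1% |

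Simulation with individual randomisation and a fully shared physician effect gave a factor of 1.007. With five separate clusters per arm it gave 1.246. Both agree with the formula.

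**Step 4: power with no design effect.**

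| Total | One-sided 0.025 | One-sided 0.05 |
|---|---|---|
| 210 | 70.5% | 80.3% |
| 260 | 79.4% | 87.2% |
| 266 | 80.3% | 87.8% |

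If the full 1.25 scenario were taken seriously at the stated alpha, the same equation with n0 = 133 gives 133 × 0.99/(1 − 133 × 0.01/5) = 131.67/0.734 = 179.4 per arm, about 359 in total.

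**The case against.** The best defence is that the clustering step is arithmetically consistent and may be deliberate caution. The protocol is concerned with a team that delivers the intervention, and it lets the physician choose to see a remote-arm patient in person, so the effect of remote care could differ between physicians. In that case a shared physician effect does not fully cancel: at a correlation of 0.5 the factor is 1.12, and at 0 it is the 1.25 used. A GEE clustered by physician would pick up such variation, so planning and analysis need not conflict. It is also true that no text says outright that the same physicians treat both arms; this is the natural reading, not a stated fact. The practical effect on the total is small, since 260 is within 3% of 266, and 266/25 = 10.6 months is still about 11 months.

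Most of this stands. It makes 1.25 the conservative end of a range, not an impossible value. It does not supply the missing assumption, and it does nothing for the base of 210.

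A reader might go further and infer that 1.25 is valid only if each physician serves one arm, that clustering adds nothing, and that the trial is therefore too large by 50 patients. The documents do not support that. Physicians tied to one arm would need about 353 to 359 patients, 1.25 also arises when physicians see both arms with uncorrelated effects, and the stated alpha needs about 266 before any clustering.

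**Conclusion.** The derivation needs correcting, although its final figure is close to adequate if clustering is negligible. The base understates the need at the stated alpha by 56 patients (266 − 210). The added 50 are labelled as clustering but nearly make up that shortfall. They cannot do both jobs: 260 gives about 79% power with no design effect and about 70% under the protocol's own 1.25, so on neither reading does the paragraph deliver its 80% with clustering accounted for.

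This rests on alpha being one-sided, a true difference of 0, an SD of 0.29 in both arms, and physicians seeing patients in both arms. The power figures do not deduct the loss of about 2% that the protocol attributes to its interim futility rule. Nothing here supports stopping at 210, where power is about 70% at the stated alpha.

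**What to change.** - Recompute the base at the stated alpha: about 133 per arm (266) with the stated SD and margin, and state that a true difference of 0 is assumed.
- If 260 is kept, give its power as about 79% with no design effect, falling to about 70% if the full 1.25 applies.
- Say whether the same physicians treat both arms. Then either drop the 1.25 factor, or state that it represents physician-by-arm variation and show it as a sensitivity scenario.
- Reconcile the 210 in Treatment Assignment with the total in the Power analysis, and do so upwards.

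The physician-clustered GEE can stay; replacing it with physician fixed effects and patient-level robust standard errors would be a matter of preference. The cost is a text amendment and, if 266 is adopted, six more patients than the stated 260, about a quarter of a month at 25 per month.
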